### Study objectives

The primary objective is to assess if 6 weeks of CMC1 joint distraction is not inferior to a duration of 8 weeks. Our primary outcome is physical function measured with the Patient-Reported Outcomes Measurement Information System Physical Function for the Upper Extremity (PROMIS UE) at 1 year after distraction.

Our secondary objectives are:
We hypothesize that there is no difference between groups in terms of pain intensity, patient satisfaction, joint stiffness, thumb function, range of motion, and strength at 1 year.We hypothesize that there is no difference in hand health status measured with the Michigan Hand Outcome Questionnaire (MHQ) between the 6-week and 8-week group at 1 year.We will investigate if there is a difference in adverse event rate and treatment failure at 1 year.We will measure minimal joint space width on radiographs at 1 year and test if there is a difference between the two groups.We will assess symptoms of depression and catastrophic thinking (captured by 2 short questionnaires) since there is mounting evidence that psychosocial factors influence symptom intensity and magnitude of physical limitations among patients with CMC1 OA [20–22]. We will test if these, and other factors, are independently associated with physical function and hand health status.To study the long-term effects of joint distraction in the treatment of CMC1 OA, we will test all hypotheses mentioned above at 2 years and 5 years post-distraction.

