#### Secondary study parameters

Patient characteristics: gender, age at operation, work status, marital status, and level of highest education.Michigan Hand Outcome Questionnaire (MHQ - Dutch Language Version): a validated 57-item questionnaire that gauges hand health status on a scale from 0 to 100 with higher scores indicating better hand health status [26].Patient Health Questionnaire (PHQ-2): 2-item questionnaire with scores from 0 representing ‘lowest level of depression’ to 6 ‘highest level of depression’ [27].Pain Catastrophizing Scale (PCS-4): 4-item questionnaire rated on a 5-point Likert scale with scores ranging from 0 indicating ‘no catastrophic thinking’ to 16 ‘worst possible catastrophic thinking’ [28].Visual analogue scale (VAS) scores for pain, patient satisfaction, thumb stiffness and function: with scores from 0 representing ‘no pain at all’ or ‘fully satisfied’ or ‘no stiffness at all’ or ‘optimal function’ to 100 ‘worst pain possible’ or ‘not at all satisfied’ or ‘worst stiffness possible’ or ‘worst possible function’.Range of motion obtained by an independent certified hand therapist:Thumb opposition by Kapandji scores (range 0–10)Palmar thumb abduction (degrees) by Pollexograph [29]Strength measures* (in kg) obtained by an independent certified hand therapist:Grip strength measured with a Jamar hand dynamometerKey and tip pinch strength measured with baseline pinch gauge**Strength measures are recorded as the average of three attempts*Radiographs will be obtained in three different views (posteroanterior, lateral and Bett’s view). Joint space (in mm) will be scored by an independent blinded radiologist.Adverse events: classified according to the Clavien-Dindo classification of surgical complications ranging from grade I (minor complication) to grade V (death) [30]. Any adverse event that occurs during the distraction period or at follow-up will be administered and classified. For example, pin tract infections that are adequately treated with oral antibiotics will be classified as grade I (minor complication). In the unlikely event that intravenous antibiotics and a hospital admission is needed, this will be rated as a grade II complication.Treatment failure: defined as conversion to an invasive surgical procedure (f.e. trapeziectomy) after distraction therapy due to ongoing symptoms of CMC1 OA.

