### Statistical analysis

The following characteristics will be reported in the baseline characteristics table: age, gender, work status, marital status, level of education, PROMIS UE scores, MHQ, PHQ-2, PCS-4, VAS for pain, satisfaction, thumb stiffness, thumb function, range of motion, strength, and joint space width on radiographs. Testing for differences in baseline characteristics among groups will only be done if visual inspection of the results indicates possible significant differences.

The primary outcome will be the difference in PROMIS UE score between the 6-week group (A) and 8-week group (B) at 1 year follow-up. We will report the mean with SD and 95% CI and the mean difference with 95% confidence interval. If the mean difference with 95% CI falls within the predefined non-inferiority margin of 9.0 points of PROMIS UE scores, we will conclude non-inferiority.

Regarding the secondary hypotheses, we will test for superiority between the 6-week and 8-week group.
We will assess any differences in MHQ scores, VAS pain, VAS satisfaction, VAS function, VAS stiffness, range of motion, and strength at 1 year follow-up compared to baseline. We will test for superiority between groups by comparing the mean differences at 1 year.Treatment failure is scored when a patient proceeds with an invasive surgical procedure (f.e. trapeziectomy) after distraction therapy due to ongoing symptoms of CMC1 OA. We will analyse the difference between groups in the proportion of participants who are classed as treatment failure at 1 year.Adverse event rates will be reported and classified according to the Clavien-Dindo classification of surgical complications. We will analyse the difference between groups in the proportion of participants who are classed as adverse event at 1 year.Joint space width at 1 year follow-up is compared to baseline measures in both groups. Mean difference in mm between groups is assessed at 1 year follow-up.

This will be intention-to-treat analyses. In case of non-adherence, to test the robustness of our results, we will also report the results of per-protocol analyses [33].

We will create 2 multivariable linear regression models to assess factors independently associated with PROMIS UE and MHQ scores at 1 year. In these models, we will include all mentioned study parameters (except PROMIS UE and MHQ scores) with *P* < 0.10 in bivariate analysis. *P* values < 0.05 are considered statistically significant.

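### The 1-year association models screen about 19 parameters at P < 0.10 in about 64 patients, with no baseline score or arm forced in and no time point set, so false or uninterpretable independent factors are likely

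*Protocol article*

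**What the plan says.** Study objectives makes this a listed secondary objective. After naming depression and catastrophic thinking, it states: "We will test if these, and other factors, are independently associated with physical function and hand health status".

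Statistical analysis gives the method: "We will create 2 multivariable linear regression models to assess factors independently associated with PROMIS UE and MHQ scores at 1 year". Selection follows: "In these models, we will include all mentioned study parameters (except PROMIS UE and MHQ scores", restricted to those with P "< 0.10 in bivariate analysis". P "values < 0.05 are considered statistically significant", and no adjustment for the number of factors is stated. The same analyses are to be repeated at 2 and 5 years, which makes 2 × 3 = 6 models.

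The candidates come from Secondary study parameters. That list opens with "Patient characteristics: gender, age at operation, work status, marital status, and level of highest education", includes the two psychological scales ("Patient Health Questionnaire (PHQ-2): 2-item questionnaire" and "Pain Catastrophizing Scale (PCS-4): 4-item questionnaire"), and runs on to VAS scores, motion, strength, joint space, adverse events and treatment failure. Treatment group is not on it. Baseline PROMIS UE and MHQ are collected, since both stand in the planned baseline table.

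**The concern.** The article does not leave model building open. It states a selection rule, and the rule has four weaknesses.

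- It screens many candidates on P values and then tests the survivors on the same small sample.
- Read literally, it removes the outcome's own baseline score. A factor that merely tracks starting function can then look independently associated with function at 1 year.
- It does not guarantee that the randomised arm is in the model.
- It names no time point. Adverse events and treatment failure can only arise after surgery, yet they qualify. VAS function, pain and stiffness are measured at baseline and at follow-up, and a 1-year VAS function score comes close to restating 1-year PROMIS UE.

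What is at stake is the answer on PHQ-2 and PCS-4. The Discussion hopes this will improve understanding of psychosocial factors and mentions future work on coping strategies. Under this rule, a link with psychosocial state cannot be told apart from worse starting function.

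**Working it through.** **1. Patients.** The Sample size calculation gives a margin of 9.0, SD 11, one-sided 2.5% and 90% power. Per arm: 2 × (1.960 + 1.282)² × 11² / 9² = 31.4, so 32, or 64 in total. Allowing for 5% loss: 64 / 0.95 = 67.4, so 68. This reproduces the planned size and gives about 64 evaluable patients.

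**2. Candidates.** From Secondary study parameters without MHQ: 5 patient characteristics + PHQ-2 and PCS-4 (2) + VAS scores (4) + Kapandji and abduction (2) + grip, key pinch and tip pinch (3) + joint space (1) + adverse events and treatment failure (2) = 19. That is 64 / 19 = 3.4 patients per candidate, and fewer once categories are dummy-coded.

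**3. No true predictor.** On average 19 × 0.10 = 1.9 candidates pass the screen. The stated rule (bivariate P < 0.10, then multivariable P < 0.05) was simulated with n = 64. The documents give no correlations among candidates, so these are assumed:

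| Common correlation | At least one false factor, per model |
|---|---|
| 0 | 57–58% |
| 0.3 | 28–29% |
| 0.5 | 14–16% |

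The ranges reflect repeat simulations. For comparison, 19 independent tests with no screen give 1 − 0.95¹⁹ = 62%.

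**4. PCS-4 without the baseline score.** Assume PCS-4 correlates −0.4 with baseline PROMIS UE, baseline correlates 0.5 or 0.6 with the 1-year score, and PCS-4 has no further effect. Its correlation with the outcome is then −0.4 × 0.5 = −0.20 or −0.4 × 0.6 = −0.24. By Fisher's z with √(64 − 3) = 7.81:

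- 0.2027 × 7.81 = 1.58, so rejection is about 35%.
- 0.2448 × 7.81 = 1.91, so rejection is about 48% (48–50% in simulation).

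Those figures suppose that no other candidate stands in for starting function. Adding baseline candidates that correlate 0.5–0.7 with baseline PROMIS UE (assumed) and applying the stated rule:

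| Other stand-ins in the pool | PCS-4 flagged, full range | Near the middle of the range |
|---|---|---|
| 2 | 9–24% | about 14–16% |
| 4 | 5–16% | about 8–10% |

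With the baseline score in the model, the rate is 5%.

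**5. Many baseline proxies at once.** Suppose 9 of the 19 candidates correlate 0.3–0.5 with baseline, and baseline alone drives the outcome (correlation 0.3–0.6). The chance that at least one proxy is declared independent is 38–77% without the baseline score and 20–23% with it. The chance of any false factor falls from 57–84% to 38–47%. The screen was kept in both cases, so restoring the baseline score alone does not cure the problem.

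**6. If 1-year VAS scores were entered.** This is an illustration. A baseline predictor correlates 0.4 with true 1-year function, on which PROMIS UE loads 0.85 and four VAS scores load 0.7. Detection of the predictor falls from 80% to 14%, and at least one VAS score is significant in 99% of runs.

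**The case against.** Several points on the other side stand.

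- **Most of the pure-null risk is plain multiplicity.** Without screening the figure is 62%, so the screen slightly lowers it. In the uncorrelated simulation, 0.85 false factors out of 19 is 4.5% per candidate, just under nominal. The distortion from selecting and testing on the same data is real, but these figures do not measure it. A fixed six-term model would itself give 1 − 0.95⁶ = 26% if all terms were null.
- **Uncorrelated candidates are implausible.** VAS, strength and psychological scales will correlate among themselves. A reader might infer that the models are bound to produce false predictors. The range in step 3 does not support that.
- **The text gives no time point.** A reader might infer that baseline scores were deliberately dropped, or that 1-year VAS values will be used. Neither is stated. The exclusion may be meant only to keep the two follow-up outcomes out of each other's models, and the fuller protocol may say so. That does not rescue the sentence: Statistical analysis uses the same names for the baseline values and then excludes them without qualification, and adverse events and treatment failure qualify on any reading.
- **The aim is association.** A reader might take the objective as causal, but Study objectives does not claim that. If catastrophic thinking itself lowers baseline function, adjusting for baseline removes part of the link. This is a reason to say which association is meant.
- **Which factors to keep is partly a matter of preference.** That choice belongs to the investigators.

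**Conclusion.** The concern holds as a defect in a stated rule for a secondary objective. The article fixes a P-value screen of 19 candidates in about 64 patients, leaves out the baseline score as the sentence reads, does not secure the arm, and admits variables that arise after treatment.

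The likely result is false or uninterpretable factors. If nothing matters, the chance of at least one per model is about 15% to 58%. A PCS-4 with no effect beyond baseline function is flagged in roughly 8% to 49% of trials, against a nominal 5%; the lower end approaches 5% where several strong stand-ins are present. Both ranges rest on assumed correlations, because the documents give none. The upper ends require uncorrelated candidates and no other stand-in for starting function, respectively. The opportunity for error recurs over six models.

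The primary non-inferiority comparison does not use these models and is unaffected. The change should be made, but the trial's main conclusion does not depend on it.

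**What to change.** Amend the model paragraph in Statistical analysis to say that:

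- only baseline values are candidates, and adverse events, treatment failure and all other post-treatment measures are excluded;
- the exclusion of PROMIS UE and MHQ applies to follow-up scores;
- each model always contains the outcome's own baseline score and the allocated arm;
- the P < 0.10 screen is replaced by a short list of baseline factors, fixed in advance by the investigators and including PHQ-2 and PCS-4, all entered together;
- estimates are reported with 95% CIs and labelled exploratory, at 1, 2 and 5 years.

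Six terms in all, for example, would give 64 / 6 = 10.7 patients per term. The cost is wording only, since the baseline measures are already collected. The downside is that fewer factors are explored. Some multiplicity remains, which is why the exploratory label is needed.

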### Randomization and blinding

Patients will be randomized to one of two groups at a 1:1 allocation ratio. We will use Research Electronic Data Capture (REDCap), a secure web-application and electronic platform for managing clinical research data [31], for randomization and allocation concealment. A fixed block size design will be generated in this secure web-application by the coordinating investigator who is not involved in patient care or in the assessment of the postoperative outcomes. Details about the randomization method or block sizes will not be available to or shared with those who enroll participants, assign interventions, or assess outcomes. Once a patient has been enrolled, the research assistant will log into the secured computer system (REDCap) and assign patients to group A or B. During placement of the distractor, the hand surgeon, operating room-assistant, and nurses will not know to which group the patient is randomized. Patients cannot be blinded. Radiographs will be scored by a blinded radiologist.

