### Sample size calculation

We aim to assess non-inferiority of 6 weeks distraction compared to 8 weeks measured by PROMIS UE scores. We performed a sample size calculation based on the minimal clinically important difference (MCID) of the PROMIS UE questionnaire. The MCID is the smallest difference that patients perceive as beneficial. Previous studies report a MCID of 9.0 points for PROMIS UE with a standard deviation of 11 [32]. Non-inferiority will be considered if the mean difference with 95% confidence interval (95% CI) is no more than 9.0 points lower in the 6-week group compared to the 8-week group. To detect non-inferiority with 90% power, and a one-sided confidence level set at 97.5%, and 5% estimated loss to follow-up, we aim to include 68 patients. Each month, it is estimated that 4 patients will be eligible and willing to participate, resulting in an inclusion time of 2 years.

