We will perform the same statistical tests and analysis as mentioned above at 2 years and 5 years post-distraction to study the long-term results. Incomplete data will be adequately described. We will use multiple imputation for any missing data or means for missing values.

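### Means are allowed in place of multiple imputation without excluding the 1-year PROMIS UE score, where they would make the deciding confidence interval too narrow

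*Protocol article*

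**What the plan says.** The Statistical analysis section of the Protocol article closes with its rule for incomplete data: "We will use multiple imputation for any missing data or means for missing values". It does not say which variables each method serves, whether the mean is that of the arm, of all patients or of a patient's other items, or when one method gives way to the other.

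The primary comparison is defined in the same section: "The primary outcome will be the difference in PROMIS UE score between the 6-week group (A) and 8-week group (B) at 1 year follow-up". The decision rule is "If the mean difference with 95% CI falls within the predefined non-inferiority margin of 9.0 points of PROMIS UE scores, we will conclude non-inferiority". The primary analysis is by intention to treat. The one robustness analysis named, per protocol, is for non-adherence and not for missing outcomes.

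The Sample size calculation section supplies the design figures: "Previous studies report a MCID of 9.0 points for PROMIS UE with a standard deviation of 11", "a one-sided confidence level set at 97.5" per cent, "To detect non-inferiority with 90% power", and "5% estimated loss to follow-up, we aim to include 68 patients".

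**The concern.** Non-inferiority turns on one limit of one interval. A mean put in place of a missing score raises the apparent sample size without bringing information, so the interval comes out narrower than the data justify. If the mean of all patients is used, part of each arm is also set to a common value and the difference shrinks towards zero. Both effects make it easier to conclude that 6 weeks is non-inferior when it is not.

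This goes beyond detail that an article leaves to a fuller document. The article positively permits a weak method, and its wording does not keep that method away from the primary outcome. An intention-to-treat analysis also gives a direct reason to fill in missing 1-year scores.

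**Working it through.** **Inputs.** Margin 9.0, SD 11, one-sided 2.5%, power 90% and loss 5% (Sample size calculation); 1:1 allocation (Randomization and blinding), so 68 / 2 = 34 per arm.

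**1. The plan's own figure.** n per arm = 2 × (1.960 + 1.282)² × 11² / 9² = 31.4, rounded up to 32, or 64 in total. 64 / 0.95 = 67.4, rounded up to 68. The stated 68 is reproduced, and nothing below affects it.

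**2. Planned loss in patients.** 5% of 34 is 1.7, so 2 of 34 per arm (5.9%) is the nearest whole number. Higher rates, 5 of 34 (15%) and 7 of 34 (21%), are assumptions about three and four times the planned loss.

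**3. Standard error with arm-mean filling.** Let k be the number observed per arm.

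- Correct SE = 11 × √(2/k)
- Reported SE = 11 × √[((2k − 2)/66) × (2/34)], because the filled values add nothing to the sum of squares but raise the degrees of freedom to 66 and the arm size to 34

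| Missing per arm | k | Correct SE | Reported SE | Ratio |
|---|---|---|---|---|
| 2 (5.9%) | 32 | 2.75 | 2.59 | 0.94 |
| 5 (15%) | 29 | 2.89 | 2.46 | 0.85 |
| 7 (21%) | 27 | 2.99 | 2.37 | 0.79 |

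**4. Shift with overall-mean filling.** The expected difference becomes −9 × k/34: −8.47, −7.68 and −7.15 for k = 32, 29 and 27. With arm means the point estimate does not move.

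**5. One-sided error at a true difference of −9.0.** Simulation with 200,000 trials per setting, equal numbers missing completely at random in each arm, and a claim counted when the lower limit of the two-sided 95% t-interval lies above −9:

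| Missing per arm | Complete cases | Arm mean | Overall mean |
|---|---|---|---|
| 0 | 2.5% | 2.5% | 2.5% |
| 2 (5.9%) | 2.5% | 3.3% | 3.9% |
| 5 (15%) | 2.5% | 4.8% | about 7.7% |
| 7 (21%) | 2.5% | 5.9% | 11.6% |

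Repeat runs moved the overall-mean figure at 15% between 7.6% and 7.8%.

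**6. Check of the arm-mean column without simulation.** The claim is made when a t variable with 2k − 2 degrees of freedom exceeds 1.997 × ratio. For k = 32 that is 1.997 × 0.940 = 1.877 on 62 df, giving 3.3%. For k = 29 it is 1.698 on 56 df, giving 4.7%. For k = 27 it is 1.579 on 52 df, giving 6.0%. These agree with the simulated values to about 0.1 percentage points.

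Complete-case analysis keeps 2.5% throughout, so the excess comes from the filling and not from the loss of patients. With 2 of 34 missing per arm, complete-case power is still 89.7%, so the planned loss creates no need for filling by means.

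**The case against.** The strongest reply is that the sentence may not concern patient-level outcomes. It names multiple imputation first, and the instruments have many items (16 for PROMIS UE, 57 for the MHQ). Averaging a patient's other items to replace a skipped one is a plausible meaning, and its effect on the primary test would be much smaller. This stands as a possible intention, but the text does not state the restriction.

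Second, the inflation is modest at the plan's own loss: 0.8 to 1.4 percentage points above 2.5%. This stands. The larger figures need loss well above plan and are shown only as a range.

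Third, the arms are pulled together only under the overall mean, and nothing says that mean is intended. This also stands. The narrowing of the interval occurs with either mean.

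Fourth, the article rests on a fuller protocol (version 3.0, Trial status section), and an analysis plan may exist. Either could fix which method applies where. So a reader might infer that the choice will be made after the data are seen, or that the primary outcome will in fact be mean-imputed. The article supports neither; it shows only that its wording permits the second. For the same reason the absence of an imputation model or a missing-data sensitivity analysis from the article is not a fault.

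**Conclusion.** The point holds in a limited form. As worded, the rule allows means for the 1-year PROMIS UE score, and using them there would break the stated one-sided 97.5% confidence level in the direction of the trial's hoped-for conclusion. Near the planned loss the error is about 3.3% or 3.9% instead of 2.5%. Only at three to four times that loss does it reach about 4.8% to 11.6%.

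These figures assume SD 11, equal numbers missing in both arms, data missing completely at random, and an unadjusted two-sample comparison. Missingness related to outcome was not examined and could change the size. A reader might take the 21% scenario as an expected result, but the planned loss does not support that. This should be fixed before analysis; it does not undermine the design or the sample size.

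**What to change.** Remove the means option for patient-level outcomes. State multiple imputation, carried out within arm, as the single method for missing 1-year PROMIS UE, using baseline and any earlier PROMIS UE scores that are collected. The Postoperative appointments and measurements section says only that several questionnaires are completed at 3 and 6 months, and the schedule figure is not visible here, so availability of PROMIS UE at those visits needs checking. If means were intended for single missing items within a questionnaire, keep the phrase and restrict it to that use.

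The cost is one sentence, a little analysis work and a slightly wider interval. With 2 of 34 missing per arm, the half-width under arm-mean filling is 1.997 × 2.59 = 5.2 points, against 1.999 × 2.75 = 5.5 points for complete cases. No extra patients are needed. A sensitivity analysis that lowers the imputed 6-week scores by a fixed amount would be a useful option but is not required to resolve the point.
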